##### Exclusion criteria

Patients who have previously sought treatment for this illness from a normal clinic (not a specialist COVID-19 clinic).Patients who are unable to provide fully informed consent (eg, dementia, psychosis or severe depression).Patients who are pregnant.

Patients without bacterial infections, immunocompromised patients and patients with non-infective conditions are not excluded from this study if they present with any of the symptoms listed in the inclusion criteria. Patients who previously sought treatment for the same episode of illness in other health services (outpatient clinic in the county hospitals, etc) will be excluded, simply because the treatment sought elsewhere may bring interference or contamination to our study findings by having previously obtained antibiotics elsewhere.

### Randomisation, allocation and blinding

All the recruited township health centres will be stratified by above or below the average baseline antibiotic prescribing rate and randomised, in blocks of 4 and 6, at a 1:1 ratio to the intervention or usual care group. Antibiotic prescribing rate (%) of each township health centre will be measured by dividing the total number of RTI patients who are prescribed antibiotics (intravenous and oral) against the total number of RTI patients who are present to each township health centre.

All participating health centres will be allocated to a trial arm at the same time, after completion of baseline data collection. Due to the nature of the intervention, it is not possible to blind practitioners to their allocation to either intervention or usual care group. However, the statisticians conducting the analysis will remain blind to allocation until quantitative analysis is complete. The trial randomisation and blinding will be conducted by an independent statistician.

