### Participants and recruitment procedures

### Selection of township health centres

We originally started the trial recruitment at village clinic level. However, in May 2021, there was a small local COVID-19 outbreak in Anhui Province, since when village clinics have not been allowed to treat RTI patients in Anhui and our trial recruitment had to be postponed. Currently, patients with suspected COVID-19 symptoms (specifically patients with a temperature of more than 37.3°) must be referred to specialist COVID-19 clinics or specialist COVID-19 hospitals for treatment. We did some preliminary fieldwork in June 2021 and found it is still very difficult to recruit RTI patients at village clinic level and the research team assessed that this situation may not change within the next 12 months. However, we found that township health centres are still able to treat RTI patients regularly. In order to complete recruitment and maintain trial feasibility, we therefore decide to change the recruitment sites from village clinics to township health centres.

We will recruit 40 township health centres from 10 counties (4 township health centres per county), those counties will be randomly selected from 4 regions geographically dispersed across Anhui Province. We will randomly recruit 6 counties from two regions in densely populated North Anhui and four counties from another two regions from sparsely populated South Anhui. We will seek support from local county health authorities during the recruitment of township health centres. They will provide a list of townships in their area and the research team will randomly select four township health centres. Local county health authorities will screen the selected townships and may exclude selected townships, for which a reason will be recorded.

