### Recruitment of practitioners

The recruitment of health practitioners will be fair. Once a township health centre is recruited and has given permission for its staff to participate, all the practitioners working in the recruited township health centres will be invited to participate in the study. Once practitioners are identified and recruited, informed consent (online supplemental appendix 1) will be obtained immediately.

10.1136/bmjopen-2020-048267.supp1Supplementary data

Exclusion criteria

Practitioners who do not have basic computer skills.Practitioners who are not involved in clinical diagnosis and medicine prescribing.

The background information of participating township health centres and practitioners will be collected. A senior practitioner in the recruited township health centre will complete a clinic background information questionnaire (online supplemental appendix 2); and all practitioners working in the clinic will give their demographic data in a practitioner background information questionnaire (online supplemental appendix 3).

10.1136/bmjopen-2020-048267.supp2Supplementary data

10.1136/bmjopen-2020-048267.supp3Supplementary data

A baseline audit of 400 RTI patients across the 40 township health centres will be conducted (10 RTI patients for each township health centre). This baseline audit will only collect primary outcome data, including the antibiotic prescribing rates at each clinic. Then all the township health centres will be randomised at a 1:1 ratio to usual care group versus intervention group, using the baseline antibiotic prescribing rates to balance high and low prescribing clinics between the arms. Each group will have 20 township health centres (details see figure 1).

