### Sample size calculation

Our previous study recorded an antibiotic prescribing rate of 75% for rural township health centres in Anhui province^21 28^ and a previous pilot intervention showed a reduction in antibiotic prescribing of more than 20%.^27^ There is no internationally agreed minimally important difference in antibiotic prescribing, however, we anticipate that a reduction of at least 15% in antibiotic prescribing would represent a meaningful change at the population level given the very high rates of antibiotic prescribing.

To detect a possible absolute difference of 15% in prescribing rates between intervention (60%) and control practices (75%) with 90% power and alpha 0.05, we will need 203 patient consultations for infection RTI in each arm. Based on our previous study results the estimated ICC value was 0.05 and a design effect value would be 2.45. We would, therefore, aim to recruit at least 2.45*203*2=995 patients into the study. Allowing for a loss to follow-up rate of 10% and a cluster size of 30 patients per township health centre, we will recruit 40 township health centres into the study and each arm will have 20 township health centres.

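### Blocks of 4 and 6 within two strata of uncontrolled size do not guarantee the stated 20 centres per arm and ignore county, although all 40 centres are allocated at once

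*Protocol article*

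**What the plan says.** All of this is in the Protocol article.

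- *Randomisation, allocation and blinding*: centres are "stratified by above or below the average baseline antibiotic prescribing rate and randomised, in blocks of 4 and 6, at a 1:1 ratio". On timing: "All participating health centres will be allocated to a trial arm at the same time, after completion of baseline data collection". An independent statistician carries out the randomisation.
- *Recruitment of practitioners*: the baseline audit takes "10 RTI patients for each township health centre", and allocation proceeds "using the baseline antibiotic prescribing rates to balance high and low prescribing clinics between the arms". Then: "Each group will have 20 township health centres".
- *Sample size calculation*: "we will recruit 40 township health centres into the study and each arm will have 20 township health centres".
- *Selection of township health centres*: "We will recruit 40 township health centres from 10 counties (4 township health centres per county"), and "We will randomly recruit 6 counties from two regions in densely populated North Anhui and four counties from another two regions" in sparsely populated South Anhui. That makes 24 North and 16 South centres. County health authorities supply the township lists and may exclude selected townships.
- *Data analysis*: a logistic mixed model with a random effect for clinic, adjusted for the clinic-level baseline rate. The full covariate list is left to the statistical analysis plan.

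No section names county or region as an allocation factor.

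**The concern.** Permuted blocks keep arms level while units enter one after another. Here nothing enters sequentially, because every centre and its baseline rate is known before the first allocation. Two consequences follow from using blocks anyway.

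1. A split at the average gives strata of whatever size the audit happens to produce. An odd stratum cannot be filled with complete blocks of 4 and 6, so a block is cut short and the arms need not come out at 20 each, as two other sections state.
2. The sampling design builds in a natural matching unit, four centres per county under one health authority, and the allocation discards it. A county that lands wholly in one arm offers no within-county comparison, and later modelling cannot restore one. The only stratifier is a two-way split of a rate from 10 patients, so it cannot be relied on to balance county indirectly.

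At stake are agreement between the article's own statements, face validity of the arms, and some precision.

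**Working it through.** **The plan's own sample size.** For 75% v 60%, 90% power and two-sided alpha 0.05 (sidedness assumed), the usual two-proportion formula gives 203 per arm. The design effect is 1 + 29 × 0.05 = 2.45, and 2.45 × 203 × 2 = 994.7, or 995. Allowing for 10% loss, 995 / 0.9 = 1106 patients, and 1106 / 30 = 36.9 centres. The 40 centres cover this. The sample size reproduces and is not at fault.

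**Arm sizes.** The stated rule was simulated with 40 centres, a 10-patient audit, mean rate 75%, ICC 0.05, beta-binomial rates, and block size 4 or 6 drawn with equal chance. The article does not say how block sizes are chosen, so the last input is an assumption.

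- Upper stratum: 16 to 27 centres (2.5th to 97.5th percentile); odd in about 50% of draws.
- Exactly 20:20: about 55% overall, made up of 0.60-0.63 when both strata are even and 0.47-0.49 when both are odd.
- Within one centre (19 to 21): about 98%. Extreme seen: 17:23.
- If the statistician instead chooses block sizes to fill each stratum, even strata give exactly 20:20. Two odd strata each leave a surplus of one centre in a random direction, so they give 20:20 half the time and otherwise 19:21. Overall that is 0.5 × 1 + 0.5 × 0.5 = 0.75.

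**Power by split** (30 per centre, design effect 2.45): 94.6% at 20:20, 94.5% at 19:21, about 94.4% at 18:22, about 94.1% at 17:23. With 27 per centre: 93.7% at 20:20 and about 93.1-93.3% at 17:23.

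**County.** Under a plain 20:20 split, the chance that a given county is 4:0 or 0:4 is 2 × C(36,16) / C(40,20) = 0.106, so 10 × 0.106 = 1.06 such counties are expected. The chance of at least one is 1 minus the coefficient of x^20 in (4x + 6x² + 4x³)^10 divided by C(40,20), which is 0.655. Simulating the stated rule with list order unrelated to county gives 0.65-0.66. If the list runs in county order it is 0.42. The North split is 15:9 or worse in about 11-12% of draws under the stated rule with random order.

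**Precision**, per centre mean on a total-variance scale of 1, assuming stable centre rates:

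- Follow-up mean (30 patients): 0.05 + 0.95/30 = 0.0817.
- Baseline mean (10 patients): 0.05 + 0.95/10 = 0.145. Reliability is 0.05/0.145 = 0.345.
- Residual variance after the planned baseline adjustment: 0.0817 − 0.05²/0.145 = 0.0644.
- With 2:2 allocation and a county term, where county carries a share s of the 0.05, let w = 0.05(1 − s). The residual is w + 0.0317 − w²/(w + 0.095).

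| s (assumed) | residual | reduction from 0.0644 |
|---|---|---|
| 0.2 | 0.0598 | 7% |
| 0.4 | 0.0545 | 15% |
| 0.6 | 0.0482 | 25% |

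A simulation with baseline adjustment in both designs, which also pays for estimating the extra terms, gave about 6%, 12% and 20%, and a loss of about 2% at s = 0. Together the range is about 6-25%.

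**The case against.** The strongest reply is that this is a valid stratified, blocked cluster randomisation that already stratifies on, and adjusts for, the baseline value of the primary outcome. Much of that stands, and it rules out several stronger readings.

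- *That the rule fails to deliver 20 per arm.* It often does deliver, and it misses by more than one centre in only about 2% of draws. The article does not say that block sizes are random, and chosen blocks do better. The supportable statement is that 20:20 is not guaranteed.
- *That power rests on 20 per arm.* It does not. Power stays near 94% at any plausible split, against a 90% target.
- *That one-arm counties bias the result.* They do not in expectation, because allocation remains random. About one county in ten is affected on average, and fewer if the list runs in county order.
- *That the model wrongly omits county.* The article leaves the covariates to the statistical analysis plan, which is not at hand, so a missing county term is no fault here.
- *That variance would fall by 12-37%.* This comes from multiplying the unadjusted between-clinic share, 30 × 0.05 / (0.95 + 30 × 0.05) = 0.61, by a county share of 0.2 to 0.6. It ignores the planned baseline-rate adjustment, which already absorbs part of any stable county difference.
- *That local COVID restrictions differed between counties at trial sites.* The article describes the village-clinic restriction as applying in Anhui generally and reports that township centres could still treat these patients.

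The reply does not remove two facts. The allocation rule is fixed in the article, not deferred, and it neither guarantees the stated arm sizes nor uses the county structure that the sampling creates.

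**Conclusion.** The point holds as an inexpensive improvement and a small internal inconsistency. It is not a threat to validity or power. The inconsistency is that 20 per arm is stated as certain in two sections, while the rule gives it in about 55% of allocations with randomly drawn block sizes and about 75% with blocks chosen to fill the strata.

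The county half matters more. There is about a two-in-three chance of at least one county wholly in one arm, provided list order is unrelated to county and county does not drive the baseline rate. The precision gain of about 6-25% depends on an assumed county share of 20-60% of between-centre variance and on stable centre rates. The documents give no between-county figure. If county explains nothing, the result is between no change and a loss of about 2%.

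**What to change.** Replace the blocks with a single constrained draw. In each county, two of the four centres go to each arm, which gives 6^10 = 60,466,176 candidate allocations. Keep those whose arm difference in mean baseline prescribing rate is below a limit set in advance, and draw one at random. This gives exactly 20:20, 12:12 in the North, 8:8 in the South and no one-arm county, and it uses the baseline rate as a continuous measure. A 20:20 constraint alone would not be enough, since the one-arm-county chance would stay at 65.5%.

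Reflect county in the primary model, for example as a random intercept, alongside the continuous baseline rate, because the allocation would then be balanced on it. If allocation has already taken place, report the county-by-arm table and adjust for county.

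Cost: a changed allocation program for the independent statistician, one model term and a small loss of degrees of freedom. No additional data or patients are needed.

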### Intervention

The complex intervention comprises training, peer support, a computerised decision aid, a public commitment letter and a patient leaflet. These were codesigned with practitioners and patients using the person-based approach method for intervention development.^26^

We optimised the intervention tools using qualitative research to identify barriers to acceptability, feasibility and engagement that need to be addressed. We conducted four rounds of ‘think-aloud’ interviews with 37 practitioners (15 from township health centres and 22 from village clinics) and 17 Patients in rural Anhui. Think-aloud interviews obtained detailed user views by asking practitioners and patients to view contents of our intervention tools (training materials for practitioners, peer support groups, computer-based treatment decision support system, patient leaflet). Findings were immediately tabulated and analysed to identify changes required, modified materials used for the next round of think-aloud interviews and the process repeated until participant feedback indicated no further important, feasible and appropriate changes were needed. Through this process, we created a feasible and generalisable intervention to reduce antibiotic prescribing tailored for the rural Chinese context. As an important element of the intervention, our computer-based treatment decision support system is adapted from a previous project where we set up a web-based just-in-time information system, and our colleagues had already tested the feasibility and acceptance of the system with a pilot study.^27^ Additionally, we organised several trial steering group meetings where the intervention tools and its feasibility and generalisability were intensively discussed before we launched the trial.

Intervention practitioners will receive training delivered face to face in one session by a senior clinician from a tertiary hospital. The training covers: (1) evidence about AMR in China and the link to their own practice; (2) addresses key concerns and misapprehensions; (3) details the current Chinese clinical guidelines on treatment of RTIs; (4) explains how to use the computer-based treatment decision support aid and (5) outlines communication strategies to improve patient acceptance of a non-antibiotic treatment decision.

Peer support groups will be established to connect the practitioners to others in the intervention group in order to provide peer support to each other during implementation. At the end of the training session intervention practitioners will be asked to organise themselves into peer support groups with a few practitioners in each and identify a lead for each peer support group. Peer support groups will meet via a widely used social media app in China (WeChat). The peer support group leader will schedule two structured Wechat meetings within a month after the training session. The group leader will be provided with a meeting guide to ensure a structured discussion and be responsible for setting up structured Wechat meetings of the peer support group, during which each member of the group will share their experience of applying the intervention (case discussion), discuss any problems and support each other to find solutions. Practitioners will be encouraged to contact each other outside of the scheduled meetings to ask for and provide support to each other. There will be another technical support group that will include the trial team and all intervention practitioners to provide technical assistance with intervention implementation. The senior clinician and two junior clinicians will be part of this group and be able to provide general guidance and reassurance that the intervention follows National Chinese prescribing guidance but will not provide specific clinical advice on cases.

A computer-based treatment decision support system will be installed on computers in consulting rooms in the intervention clinics. This will allow practitioners to record the patient’s symptoms and the practitioner’s diagnosis and will then provide the appropriate treatment guidance from the Chinese national guidelines. The treatment decision support system has been adapted from our previous project.^27^ It contains the following sections (online supplemental appendix 5): (1) patient eligibility criteria; (2) patient symptoms: allow practitioners to record what symptoms patients are suffering from; (3) diagnosis, patient reassurance and prognosis: allow practitioners to record their diagnosis, and provide appropriate patient reassurance and prognosis for each type of RTI patient; (4) treatment recommendations for each type of RTI patient from Chinese National Guidelines for Treating Acute Respiratory Tract Infections; (5) Table of symptomatic treatment options for RTI patients (also from Chinese National Guidelines); and (6) Safety netting advice (when to come back to see the doctor) (also from the Chinese National Guidelines).

10.1136/bmjopen-2020-048267.supp5Supplementary data

Practitioners will be required to sign a public declaration letter stating that they are committed to reducing unnecessary antibiotic prescribing and display this in a public area of their clinic.

Township health centres will be provided with a leaflet that can be given to RTI patients. This leaflet will address common patient beliefs and concerns about RTI, address common misapprehensions that can lead to an expectation of antibiotic treatment, provides advice on non-antibiotic symptomatic treatment options and safety-netting.

### Data collection methods

Baseline data will be collected for 400 patients with RTI at the participating township health centres. Follow-up data collection will be collected for 1200 patients at the participating township health centres after implementation of the intervention.

In all recruited township health centre, direct observations will be carried out by a researcher from Anhui Medical University following the doctor questionnaire (online supplemental appendix 6) adapted from our previous study.^16^ Observation will focus on the adult RTI clinical consultations and record patient symptoms, practitioner’s diagnosis & treatment, sickness severity, any antibiotics or other medicines prescribed and mode of administration (intravenous or oral), name, dosage and quantity. Immediately after the consultation, the researcher will fill in a patient questionnaire (online supplemental appendix 7) by asking questions of patients directly. This questionnaire is also adapted from the previous study^16^ and includes questions about patient demographic characteristics (gender, age, education level, residential area and medical insurance records), illness duration, symptom severity and patient satisfaction with the consultation; the latter two questions will be scored using a 10-point scale.

10.1136/bmjopen-2020-048267.supp6Supplementary data

10.1136/bmjopen-2020-048267.supp7Supplementary data

The researcher will conduct telephone interviews with recruited RTI patients at 7, 14, 21 days after their consultation. Structured questionnaires will be completed for each patient by the researcher during the telephone interview, with different secondary outcome data collected at different time points (see table 1). Illness severity (scored on a 10-point scale) and symptom duration will be recorded at each time point. Patient attitude, understanding of the patient leaflet and beliefs will be recorded once at 7 days after consultation (online supplemental appendix 8). Patient continuing illness severity and recovery situation (when they feel better and when they feel they could get back to normal) will be checked at 7 days (online supplemental appendix 8, and 14 days after consultation (online supplemental appendix 9). Patient consumption of antibiotics (including name, days, dosage and quantity) will be recorded at 7, 14 and 21 days after consultation (online supplemental appendix 10). Through checking with patient’s actual consumption of antibiotics (how many days they have taken the antibiotics, dosage etc) at different periods against the prescribed quantity of antibiotics (if applicable), patient adherence to follow practitioner’s advice (%) could be estimated. Other healthcare use (clinic visits or consumption of other treatment) will be recorded at 21 days after consultation. Patient out-of-pocket spending due to this illness, including purchase of medication, fees for clinic attendance, days off-work, will be recorded at 21 days after consultation. Patient quality of life will be measured using the EQ5D-5L during the initial consultation, at 7, 14 and 21 days after consultation. (Use of paper interview administration mode of EQ5D-5L in Chinese version has been authorised by EuroQol Group (registration ID: 32880).

10.1136/bmjopen-2020-048267.supp8Supplementary data

10.1136/bmjopen-2020-048267.supp9Supplementary data

10.1136/bmjopen-2020-048267.supp10Supplementary data

**Table 1 T1:** List of the primary and secondary outcome measures and when they will be collected at follow-up audit

Item	Outcome measure	Initial consultation	Patient telephone interview after consultation		
			7 days	14 days	21 days
Primary outcome	Prescribing rate of antibiotics (%)	√			
Secondary outcomes	Patient satisfaction	√			
	Patient symptom severity and duration		√	√	√
	Patient recovery		√	√	
	Patient consumption of antibiotics		√	√	√
	Patient attitude, beliefs and understanding of the patient leaflet		√		
	Patient costs				√
	Patient quality of life (EQ-5D-5L*)	√	√	√	√

EQ-5D-5L refers to a standardised measure of health-related quality of life developed by the EuroQol Group to provide a simple, generic questionnaire for use in clinical and economic appraisal or population health status surveys. The descriptive system comprises five dimensions: mobility, self-care, usual activities, pain/discomfort and anxiety/depression. Each dimension has 5 levels: no problems, slight problems, moderate problems, severe problems and extreme problems.

